**ENROLMENT**				
Eligibility screen	X			
Informed consent	X			
Allocation	X			
**INTERVENTIONS**				
*Supported Education - coaching*			X	X
*Control intervention*			X	X
**ASSESSMENTS**				
**Demographics**				
*Age*				
*Gender*				
*Cultural background*	X		X	X
*Diagnosis (and age of onset)*				
*Treatment*				
*Medication use and type*				
*Type, year and level of education*				
*Hours spent on education*	X		X	X
*Employment*				
**Remaining at school**			X	X
**Student success**				
*(GPA, number of courses and credits completed)*	X		X	X
**Student satisfaction**				
*The students’ life satisfaction questionnaire – school subscale*	X		X	X
**Other measures**				
*List with study skills*	X		X	X
*List with resources*	X		X	X
*The General Self-Efficacy scale*	X		X	X
*The Working Alliance Inventory*			X	X
**Psychological distress**				
*Symptom Checklist − 10*	X		X	X
**Evaluation**			X	X
*Interview*		X		
*Focus groups*				X
**Fidelity**				
*Interview*			X	

The quantitative data will be collected online for both sites by the data coordinator using online questionnaires through Enalyzer (a secure software program for research purposes). The data in Enalyzer will be linked to the student ID for this study so that the answers are not linked to identifiable information. All data will be handled confidentially in compliance with the Dutch Personal Data Protection Act (Wet Bescherming Persoonsgegevens; WBP). All data will be stored and locked at the Hanze University of Applied Sciences Groningen and will be destroyed ten years after finishing the study.

Students are blinded for which type of intervention is the experimental/control intervention. They are told that we will compare two types of support services of which they will receive one. The data coordinator who will perform the randomization process is obviously not blinded as is the researcher who will conduct the interviews about the support with the students afterwards. However, they have no personal interest in the outcomes.

### Interventions

#### Experimental condition: supported education- coaching

SEd is a tailor made, personalized intervention, taking the individual’s own educational goal as starting point of the intervention and helping the student assessing the personal critical skills and supports to achieve the personal educational goal. It is a manualized psychiatric rehabilitation intervention suitable for different mental health and educational contexts (see [20, 42, 43] for a detailed description of the SEd intervention). The SEd intervention consists of five steps:
Helping the student setting his/her own educational goalIdentifying the critical skills and support that the student needs to be successful and satisfied at his/her school of preferenceWriting the Individualized Study Support Plan. This plan defines what the needed and critical skills and support are to be successful and satisfied at school and how to respectively teach and organize them.Teaching the student the critical skills (cognitive, social and emotional)Organizing the critical support (people, places, activities, things and accommodations)

The student has regular meetings with the SEd specialist. These meetings take place in person, online or by telephone, depending on the preference and the schedule of the student.

The SEd specialist in this study is an educational professional who has been trained for at least three days in the ‘keep phase’ of SEd as described in the Handbook Supported Education [42].

#### Control condition: support as usual plus advice on potential supportive resources

Students in the control condition get support as usual plus advice on potential supportive resources. At Mbo Utrecht, students in this condition meet on a regular basis with their own student service provider who advices them about regular supportive resources that are in place at the educational institute. At the Hanze University, there are no student service providers with comparable tasks, therefore an educational staff member has been trained on giving advice to students about potential supportive resources. In three face-to-face meetings and two consults by phone, this staff member provides the students in this condition with:
Information on formal and informal support opportunities inside and outside the school (e.g., contact with a fellow student or a family member or a consult with a disability support service member or a psychologist)Basic information on studying with mental health problems (e.g., rights and responsibilities of students, students’ stories of studying with mental health problems)Information on assistive technology and sources

Subsequently, the student decides for himself whether he follows the advice of the staff member. It is recorded by the student service providers (at Mbo Utrecht) and the staff member (at the Hanze university) how many meetings take place and what kind of support is offered.

### Measurements

A complete list of measurements and measure points can be found in the SPIRIT flow diagram (Table 1). At baseline and the 6- and 12-month follow-up, the following demographic information will be collected: age, gender, cultural background, type, year and level of education, number of hours spent on education per week (i.e., school hours and homework), employment information (number of hours), diagnosis (including age of onset), treatment, medication use and type of medication, and psychological distress. The latter will be measured with the Hopkins Symptom Checklist-10 [44, 45], which is an abbreviated version of the widely used SCL-90. The SCL-90 has been validated in the Dutch language [46]. The items used in the SCL-10 are derived from this validated Dutch translation of the SCL-90, and proved to perform almost as well as another abbreviated version of the SCL-90, the SCL-25 [47]. In the study of Strand et al. [47] a large group of young adults (aged 18–24 years) participated (*n* = 877). On a 5-point scale ranging from 1 (not at all) to 5 (a lot) students indicate whether they have been hindered by symptoms or problems such as ‘Feeling tense’ and ‘Feelings of worthlessness’. The SCL-10 is included in order to describe and confirm the presence of symptoms in the population of the study and is an addition to the inclusion criteria of having a formal diagnosis or experiencing symptoms for at least six months, and receiving treatment for mental health problems or having received treatment in the past. Many research studies that do not administer symptoms checklists are speculated to recruit individuals who do not have “serious or persistent mental illnesses”. Such allegations reduce the study’s ability to generalize to the larger population of people with mental illnesses. Furthermore, this checklist will be used to verify that SEd does not have a negative impact on psychiatric symptoms and level of distress.

#### Primary study outcomes

The main outcome measure will be ‘remaining at school’. At the 6- and 12-month follow-up, it will be examined whether the student remained at school (or graduated) or has dropped-out. If students dropped-out of the study, the reason for dropping-out (voluntary, involuntary, graduation) will be checked.

#### Secondary study outcomes

Secondary study outcomes are study success and student satisfaction.

*Study success* will be measured with the following indicators: grade point average per semester; number of credits completed per semester; and number of courses completed.

*Student satisfaction* will be determined by the school subscale of the Multidimensional students’ life satisfaction scale [48, 49], which consists of eight items measuring the overall satisfaction of the student at school. Students indicate on a 4-point scale, ranging from 1 (Rarely) to 4 (Always) to what extent the statements, such as ‘I like the activities at school’ and ‘I learn a lot at school’ are applicable to them.

Furthermore, the following measures will be included in order to examine whether the scores of the students in the two conditions differ on these aspects which could account for any possible effects:
The General Self-Efficacy Scale [50, 51], which is a 10-item instrument to examine a person’s belief that his or her actions are responsible for successful outcomes, that is, that they have control over the demands of the environment. Students are asked to indicate on a 4-point scale ranging from 1 (Not at all true) to 4 (Exactly true) to what extent the items are applicable to them. Sample items are ‘ It is easy for me to stick to my aims and accomplish my goals’ and ‘When I am confronted with a problem, I can usually find several solutions’. The psychometric properties of this instrument are examined among 19,120 (young) adults from 25 countries, including the Netherlands, and proved to be good [51].The Working Alliance Inventory [52] measures the quality of the working alliance between professional and client with 36 items, divided in three subscales, bond (between professional and client), goals (agreement about the goal of the treatment) and tasks (agreement about the tasks of the treatment and the responsibilities to perform these tasks). Students are asked to indicate on a 5-point scale ranging from 1 (never) to 5 (always) to what extent the items are applicable to them. Sample items are: ‘I do not feel at ease with [-----] and ‘[-----] knows exactly what my goals are’. The Working Alliance Inventory has been translated into Dutch and has proven to have good content validity, internal consistency and construct validity among a sample of adults in rehabilitation research [53]. Students who receive the SEd intervention, answer these questions with their SEd specialist in mind; students in the control condition are asked to answer these questions with the student service provider (at Mbo Utrecht) or the educational staff member (at the Hanze university of applied sciences) in mind.A (self-constructed) checklist with 50 study skills (e.g. making notes; preparing for exams, and concentrating) which we constructed ourselves and was inspired on [54]. The student is asked to indicate for each of the study skills whether he can perform that skill or has difficulty with it. If he indicates that he has difficulty performing the skill, he is asked to indicate whether he needs support with it or already receives support with performing the skill. The student has the option of adding study skills that were not mentioned in the checklist (see Additional file 4).A checklist with 47 possible formal and informal resources, inside and outside the educational setting (e.g. study advisor; quiet room to study; note book) which was also self-constructed (see Additional file 4). The checklist consists of all available resources at the two sites, complemented with resources that are often mentioned by students in the resource assessment that we apply during SEd trajectories [42]. The student is asked to indicate which of the listed resources he needs and whether he already uses that resource or not. The student has the option of adding resources that were not mentioned in the checklist.

Both checklists are used to give a descriptive indication of the number of study skills with which students experience difficulties and the number of resources they use and need.

In addition, the number and duration of contacts with the professional (SEd specialist or the student service provider or the trained staff member) will be registered and it will be determined whether the two conditions differ in this respect.

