### Study procedures

We adhere to the SPIRIT 2013 guidelines [40], the checklist is provided in the Additional file 2.

Students who heard about the study through one of the recruitment strategies and are interested in participation, contact the research team by e-mail. A data coordinator will check the inclusion criteria and will then send a link to an online questionnaire which starts with information about the study and the question to fill out an informed consent form. In the informed consent (see Additional file 3), students state that they have been informed about the study and that they participate voluntarily. In addition, they give permission to collect grades and course credits from the school’s administration for the next five years, so we are able to follow the study success of the students after the current project has finished. They also give permission that in case they drop-out of the study, school progress keeps being monitored. Students have the right to withdraw this permission at any moment in time.

After signing the informed consent, the students fill out the baseline-questionnaire. Then, students will receive a student ID number and will be randomized, for both educational institutes separately, by the data coordinator in either the experimental condition (Supported Education-coaching; half of the group of students) or the control condition (support as usual plus advice on potential resources; half of the group of students), using the minimization approach [41] which aims to minimize imbalance between the conditions on specific factors, in our case on gender, age, ethnicity, study year, level of study, the number of credits completed, and level of psychological distress. The condition to which the student is allocated depends on the characteristics of the students that were already enrolled. Students will receive compensation (a gift coupon of 12,50 euro each) for filling in the questionnaires at baseline, 6- and 12-month follow-up. Within this 12-month follow up, each student experiences a critical moment in the educational pipeline: either transitioning to the next year or graduating. In Table 1, the Spirit flow diagram of the study procedure is presented.

**Table 1 Tab1:** SPIRIT flow diagram of the study procedure showing enrolment, interventions, and assessments

	Pre-intervention	Post-intervention (within one month)	6 month follow-up	12 month follow-up
**TIMEPOINT**	**t**_**0**_		***t***_***1***_	***t***_***2***_

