With respect to the primary outcome, remaining at school, we will compare the number of students who remained in education or graduated in the experimental and the control condition at T2. Logistic regression models will be conducted to test the differences between the experimental and control condition. In addition, the differences in scores on the secondary outcomes, study success and student satisfaction, will be examined for T0 to T2 using chi squares or repeated measures of variance with the ANOVA test using 95% confidence levels, respectively. Furthermore, the differences between the two conditions on number and duration of contacts with the SEd specialist, the trained staff member or students service provider; the number of study skills where the students need support with and the number of resources needed or used when studying, student general self-efficacy levels and the working alliance with the professional, will be calculated using the ANOVA test with 95% confidence levels. Moreover, to test whether outcomes are similar for students from both educational institutions, sensitivity analyses will be performed excluding students from the institute for intermediate vocational education.

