A bottleneck of many RCTs is the low influx of participants [62–64]. Therefore, in this study we will be attentive on the inclusion speed: can a sufficient influx of students be expected per site; is there still a willingness to participate at the various levels of the organization, and are disturbing factors for the project expected (e.g. a reorganization)? In addition, we will closely monitor the influx of students during the recruitment phase by evaluating monthly if recruitment rates are on track, in order to identify potential problems in time and initiate additional actions to boost inclusion.

In order to recruit a sufficient number of students, we asked the advisory board to advise us about relevant recruitment strategies. The recruitment strategies that were mentioned like posts on the internal website of the schools and on social media, posters, information brochures and personal contact with educational professionals will be used in the study.

To increase the chance that we reach a sufficient number of students for our study, we decided that the inclusion period of students is six months. Consequently, there will be differences at baseline being the point in the school year the student is enrolled in the study. However, we expect these differences to be the same in the experimental and control condition. We will report this information and if necessary, we will take it into account during the data analysis.

In addition, the attrition of participants can be a threat to studies in which follow-up measurements are used [63, 65]. In the informed consent form of our study, students give permission to collect information about their school progress (drop-out, grades, and course credits) from the school’s administration system also in case they drop-out of the study. In this way, complete and objective data regarding our primary outcome (remaining in school) and a part of our secondary outcomes (study success) are guaranteed.

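### Study success is counted per semester but scheduled at 6 and 12 months from rolling entry, with no rule tying semester to visit; this affects the T1 value and the T0 GPA of new students

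*Protocol article*

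**What the plan says.** Under Secondary study outcomes, the protocol article gives three indicators of study success: "grade point average per semester; number of credits completed per semester; and number of courses completed". GPA and credits are tied to a semester; the course count has no stated period.

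Table 1 lists "GPA, number of courses and credits completed" at T0, T1 (6 months) and T2 (12 months). Study procedures implies that these months run from each student's own entry: "Within this 12-month follow up, each student experiences a critical moment in the educational pipeline: either transitioning to the next year or graduating".

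The Discussion says "we decided that the inclusion period of students is six months" and accepts that "there will be differences at baseline being the point in the school year the student is enrolled in the study". It expects the differences to be the same in both conditions, and will report them and allow for them in the analysis if needed.

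Proposed analyses states that the secondary outcomes "will be examined for T0 to T2", naming chi-square tests and repeated-measures ANOVA. The inclusion criteria under Participants do not require a completed semester. The consent described in Study procedures covers school records for five years: "they give permission to collect grades and course credits".

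**The concern.** Two clocks run side by side. School results close at the end of a semester, whereas visits fall 6 and 12 months after entry, and entry is spread over half a year. Nothing in the article says which semester fills which visit.

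Two consequences follow. A value read at T1 can describe a semester that was partly over before the student was randomised. And a student who enters during the first semester has no earlier semester from which to take a T0 GPA, although T0 is one end of the planned comparison.

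At stake is the second hypothesis (higher GPA, more credits and courses under Supported Education). A weak T1 result could partly reflect calendar mixing, and new students could fall out of the GPA analysis. The primary outcome, remaining at school, is not touched.

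**Working it through.** The article gives no figure for this point, so there is none to reproduce. The check is timing arithmetic.

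**Inputs from the article**
- GPA and credits per semester; visits at 0, 6 and 12 months; a six-month entry window whose calendar start is not given.

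**Assumptions**
- Semester length S is 6 months, with 5 months as the alternative; semesters follow one another without a gap.
- A student enters m months into a semester, with m spread evenly over the semester.
- Each visit takes the last completed semester.

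**Step 1: T1 with S = 6.** The last semester closed at 6 months is the one in which the student entered. Its share before entry is m/6:

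| m (months) | 0 | 1 | 2 | 3 | 4 | 5 |
|---|---|---|---|---|---|---|
| share before entry | 0% | 17% | 33% | 50% | 67% | 83% |

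The mean is 3/6 = 50%. A six-month window covers every phase of a six-month semester once, so this mean does not depend on the calendar start. The share exceeds one quarter when m > 1.5, that is for (6 − 1.5)/6 = 75% of students.

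**Step 2: T1 with S = 5.** For m < 4 the last closed semester is again the entry semester, with share m/5 (0%, 20%, 40%, 60% at m = 0, 1, 2, 3). For m ≥ 4 a further semester has closed by month 6 (4 + 6 = 10 = 2 × 5) and the share is 0. The mean over one semester is (1/5) × ∫₀⁴ (m/5) dm = (1/5) × 1.6 = 32%. A six-month window is one five-month cycle plus one repeated month, so the exact value depends on its start. The repeated month adds between 0 (m from 4 to 5) and 0.7 (m from 3 to 4), giving 1.6/6 = 27% to 2.3/6 = 38%.

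**Step 3: T2.** With S = 6, the last semester closed at 12 months began 6 − m months after entry, which is positive for every m below 6. With S = 5, it began 5 − m months after entry for m < 3 and 10 − m months after entry for m ≥ 3. The share before entry is 0% in every case.

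**Step 4: accumulated counts.** If credits or courses are instead summed from T0 to T2, subtracting the T0 count removes what was already credited at entry. It does not remove work done before entry on courses credited afterwards. With S = 6 the entry semester is one of two closed by T2, so the share is m/12: mean 25%, range 0 to 50%.

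**Step 5: T0 for a first-semester student.** Semester GPA: none exists. Credits in a completed semester: none exists. Cumulative credits and courses: zero, a defined value. A complete-case repeated-measures ANOVA that includes T0 therefore loses the student for GPA, but not for the cumulative counts.

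**The case against.** The strongest reply is that an article need not set out how school records map to visits, and that an unstated mapping is not a wrong one. The T1 percentages do rest on a mapping and a semester length that the article does not give, and they vanish for a student who enters at the start of a semester. That much stands.

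The entry-point problem is also openly acknowledged. Randomisation should balance it, and minimisation uses study year and number of credits completed. This answers any charge of bias between the arms. It does not answer dilution at T1 or loss of students without a T0 GPA: adjusting for entry date neither changes which work a semester contains nor creates a GPA that never existed. For the same reason, the Discussion's assurance that school records secure complete study-success data cannot extend to that value.

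Read literally, the analysis sentence assigns chi-square tests to study success and repeated-measures ANOVA to satisfaction. The loss of students then depends on ANOVA, or another change-from-T0 analysis, being used for GPA. But GPA is a mean, and a chi-square test would need it to be cut into categories. Any T0-to-T2 comparison of GPA still needs a T0 value.

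Three stronger readings are tempting. A reader might infer that the T2 result is contaminated too; Step 3 shows that it is not for a last-completed-semester value, and the 25% in Step 4 belongs only to accumulated counts. A reader might infer that new students have no T0 value at all; their cumulative credits and courses are zero, not missing. A reader might infer that a standardised difference of 0.50 shrinks to 0.25 at T1; that needs an effect strictly proportional to exposure, and the article states 0.5 for the primary outcome only.

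**Conclusion.** The concern holds in a limited form. Per-semester outcomes are attached to individual 6- and 12-month visits under rolling entry, with no rule joining the two.

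- **T1:** if the last completed semester is used, on average about 50% of it (six-month semesters) or about 32% (five-month semesters) predates randomisation, given even entry. The effect is dilution, expected to be equal in the two arms, and not bias.
- **T2:** unaffected under the same rule. Only accumulated credit or course counts carry some pre-entry work.
- **T0:** students in their first semester lack a semester GPA and a completed-semester credit total. They drop out of a complete-case repeated-measures analysis of GPA. How many there are cannot be told, since neither the calendar position of the entry window nor the mix of study years is given.

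This concerns a secondary outcome. It should be settled before records are extracted, and it does not threaten the trial's main comparison.

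**What to change.** Leave the questionnaires at 6 and 12 months and define study success on the school calendar:

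1. T0 is the last semester completed before randomisation.
2. The main study-success outcome comes from the last full semester that began after randomisation and closed by T2. Where none has closed, extract the record slightly later.
3. Report the semester that straddles randomisation separately. Label any accumulated credit or course count as including work on courses begun before entry.
4. Compare the arms on the outcome in item 2, with prior GPA as a covariate plus an indicator for no prior semester, in place of change from T0. New students then stay in the analysis.

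The cost is small. Consent already covers five years of records, and with semesters of six months or less a full later semester closes by month 12 (it ends 2S − m months after entry, at most 12). Later extraction is therefore needed only where breaks or late posting of grades delay it. The real downside is that students who graduate or leave before completing a full later semester would have no value. Only those with under six months to graduation are excluded, so some such students may enrol. Their handling must be stated, for example by using their straddling semester in a sensitivity analysis.
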